### Aim 2.

This aim examines pathways through which different inoculation strategies affect distal (W5) alcohol use. Analyses in

Aim 1 serve as a baseline for examining mediation and the subsequent decomposition of intermediate effects. SEM provides a parsimonious tool

Figure 7. General model for SEM of intervening processes

[figure not shown]

that enables the analyst to identify indirect pathways of influence between intervention assignment and high school alcohol use outcomes. The potential mediators include SAAF-targeted protective processes, SAAF–Teen-targeted protective processes, and preadolescent (Wave 3) alcohol use. Figure 7 provides a general specification for intervening variable models. Baseline or pretest levels of distal and proximal processes will be controlled in all analyses. For example, in analyses of SAAF–T intervention-targeted processes as a mediator, pretest (Wave 4) levels of these processes will be controlled when testing for posttest (Wave 5) changes. Because multiple protective processes are targeted in each program, we will approach their operationalization with diverse methods. First, we will create scores that index the number of protective processes that a youth or family evinces using established cutoff scores. Such indices account for the numbers of protective factors present rather than variability in any particular factor. We have used this approach previously, and it is sensitive to intervention effects. We have also had success in forming latent constructs from sets of interrelated intervention-targeted mediators. In these analyses, we will confirm the protective processes’ underlying dimensionality and examine invariance in the protective factors’ measurement model across time. We will test uncorrelated protective processes in separate models. Significance of mediational effect tests will be assessed with bootstrapping methods per MacKinnon.

Statistical power. With Monte Carlo simulation ( $n = 100$  per group), we evaluated power to detect the significance of path coefficients that vary in their “true” magnitude, holding the other parameters in the model constant at values estimated from previous research. For the paths included in Aim 2, power ranged from .7 to .9 for detecting path coefficients ranging from .2 to .4 ( $p < .05$ ). This suggests that we will have the power to detect small and medium effect sizes among model paths.

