### Random assignment and contamination.

After pretest, families will be assigned randomly to one of four experimental groups: (a) *preadolescent inoculation*, (b) *mid-adolescent inoculation*, (c) *dual inoculation* control, and (d) control. Although the efficacy of SAAF and SAAF–Teen have been established, inclusion of a

control condition provides a baseline from which to compare normative alcohol use behavior in the population to both single- and dual-inoculation groups; it is also essential for comparing the single inoculations' economic efficiency. Preadolescent inoculation families will be assigned to receive SAAF at age 11 with no further intervention. Mid-adolescent inoculation families will receive SAAF–Teen at age 14. The dual-inoculation group will be assigned to receive both SAAF at age 11 and SAAF–Teen at age 14. The control condition involves no intervention contact. Participants will be notified if they are selected to participate in SAAF shortly after pretest. No participants will know if they are to receive SAAF–Teen until several months prior to its implementation. For each intervention implementation, families who are not attending a program receive written information by mail regarding adolescent development and alcohol use. Sending these materials is intended to maintain investment in the project for families who are not attending an intervention. No alcohol use effects are expected based on receiving written materials. All families will be followed across the course of the proposed study and assessed regardless of the number of intervention sessions they attend (intent-to-treat design). Information will be collected from family members about their participation in family enrichment programs offered in the school or community. The potential effects of participation in other programs (contamination) will be examined and statistically controlled in data analyses, as Lang et al. described.

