**Demographics (Waves 1-5).**

Primary caregivers will report their yearly income, per capita income, employment status, duration of unemployment during the past 2 years, hours worked per week, education level, numbers of children and adults in the household, and relations of all household members to one another.

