## **Data Analysis**

### **Data management, exploratory data analysis, psychometrics, and experimental considerations.**

Data will be organized and cleaned following quality control procedures that involve analyses of outliers and unexpected or inappropriate missing-data patterns. Next, items' distributions and constructs' psychometric properties will be examined. We will establish equivalence among experimental conditions with ANOVAs and chi-square tests on baseline levels of alcohol use, preadolescent protective processes, and demographic variables. Any departures from equivalence will be controlled in subsequent analyses. All primary analyses will be intent-to-treat.

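### Aim 2 tests Wave 3 drinking as a mediator of Wave 5 drinking, but the text names no control beyond baseline or pretest levels for causes shared by the two, so an early-use pathway can be declared when early use has no effect.

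*Combined protocol and SAP*

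**What the plan says.** The Aim 2 section sets out to study "pathways through which different inoculation strategies affect distal (W5) alcohol use". Its candidate mediators are the SAAF-targeted processes, the SAAF–Teen-targeted processes, and "preadolescent (Wave 3) alcohol use". On covariates it says: "Baseline or pretest levels of distal and proximal processes will be controlled in all analyses". The example that follows is specific to one mediator: Wave 4 levels of the SAAF–Teen processes are held constant when their Wave 5 levels are tested. On inference it says: "Significance of mediational effect tests will be assessed with bootstrapping methods".

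Two covariate provisions stand elsewhere. The data management section says: "Any departures from equivalence will be controlled in subsequent analyses". The random assignment section says: "The potential effects of participation in other programs (contamination) will be examined and statistically controlled in data analyses". Latent growth curves appear only under Aim 1, as something the team will consider.

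The text does not state an assumption of no unmeasured mediator-outcome confounding, does not list common causes of mediator and outcome, and plans no sensitivity analysis for the mediation results. Figure 7, the general model for these analyses, is not shown in the available text.

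**The concern.** Mediator and outcome are the same behaviour in the same youth, two annual waves apart. Family, peers, temperament and reporting style can drive both. Assignment is randomised; Wave 3 use is not. Conditioning on Wave 1 use at age 11 removes only the part of that liability which the age-11 report captures.

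The other provisions serve other purposes. A shared cause that is perfectly balanced across arms still distorts the mediator-outcome path, so adjusting for baseline imbalance does not reach it. Outside-program participation is one specific exposure. The bootstrap handles sampling error, not confounding. The paths from SAAF-targeted processes to Wave 5 use have the same gap, although their time order is right.

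At stake is the explanatory claim of Aim 2. A report that postponing early drinking lowers high-school drinking could be made when the data show only that SAAF lowered Wave 3 use and that the same youths tend to drink at both waves.

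**Working it through.** **Inputs from the documents.** Four groups; 400 of 460 families expected to complete, so about 100 per group; Wave 1 at age 11; SAAF–Teen delivered after Wave 4; SAAF efficacy taken as established.

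**Not in the documents, so assumed.** Drinking prevalence by wave, correlation between waves, and the size of SAAF's effect on Wave 3 use.

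**The plan's own figure.** Aim 2 states power of .7 to .9 for path coefficients of .2 to .4 at 100 per group. The other parameters of that simulation are not given, so it can be neither reproduced nor called wrong. (A Fisher z calculation at a total of 200 gives .81 for .2 and 1.00 for .4.) It serves below only as a scale for path sizes, read as standardised.

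**Closed form.** Let U be stable liability and T assignment, with within-arm variances of 1:

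- W1 = √l₁·U + e₁
- W3 = a·T + √l·U + e₃
- W5 = √l·U + e₅

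The true effect of W3 on W5 is zero, and so is the total effect. Regressing W5 on T, W3 and W1 gives the W3 coefficient

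b = l(1 − l₁) / (1 − l·l₁)

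| Share of variance due to U: W1 / later waves | b |
|---|---|
| 60% / 60% | .24/.64 = .375 |
| 30% / 30% | .21/.91 = .23 |
| 10% / 30% | .27/.97 = .28 |
| 90% / 60% | .06/.46 = .13 |
| 100% / 60% | 0 |

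Three of these fall in the .2 to .4 range that the plan treats as detectable. In the 60% case, a = −.2 SD gives a false indirect effect of −.2 × .375 = −.075, with an equal and opposite false direct effect of +.075. With a = 0 the indirect effect is 0, and 4-6% of simulated trials are significant. With U itself in the model, at most about 5% are.

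**Binary use, closer to the actual data.** Use at each wave is a threshold on a latent liability correlated .3 to .6 between waves. W1 use is 5% and controlled; W5 use is 40% in both arms; W3 use has no effect on W5 use. Both paths are logistic, and a pathway is declared when both are significant, which is close to the bootstrap test.

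| SAAF effect on W3 use | 100 per group | Arms pooled, 200 vs 200 |
|---|---|---|
| 15% to 7.5%, or 20% to 12% | about 16-39% | 50-70% |
| 12% to 8% | about 6-13% | 18-30% |

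At 200 versus 200 the total effect on W5 use is significant in only 4-6% of these trials. A false pathway together with a significant total effect occurs in about 1-3%.

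**Which contrasts.** Of six pairwise contrasts, SAAF differs between arms in four. In mid-adolescent versus control and dual versus preadolescent it does not differ, and SAAF–Teen comes too late to alter Wave 3 use. The assignment-to-W3 path is therefore zero by design.

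**How far covariates help** (15% to 7.5%, 200 versus 200). At a liability correlation of .45, a Wave 1 covariate sharing half its variance with liability cuts false pathways from 66% to 46%; controlling liability fully gives 3.5%. If the covariates carry only 30% of liability, about 36-71% remain across the .3 to .6 range.

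**The case against.** The strongest reply is that the covariate sentence is plural and applies to all analyses. Proximal processes could well mean the whole Wave 1 SAAF battery, including self-regulation, prototypes of drinking peers and resistance efficacy. Figure 7 might also show further covariates. Both points stand: a reader might infer that the plan omits these controls, but the documents show only that the text does not settle it. The mediator-specific example favours the narrower reading without proving it, and the simulation models that less favourable reading.

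Second, Aim 1 is already the baseline for the decomposition, so a null total effect would be visible. That is largely right. However, the plan does not make a pathway claim depend on the total effect, nor require the two to be reported together.

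Third, the 50-70% figure needs pooled arms, whereas Aim 2 states 100 per group and describes no pooling. This also stands, so the 100-per-group figures come first.

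Fourth, every prevalence and correlation is assumed. True; if Wave 1 use captured liability fully, the bias would vanish. The 60% setting is borrowed from the growth-curve reliability statement and is not a documented share of trait variance.

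**Conclusion.** The concern holds in a limited form. As the text stands, Aim 2 can declare an early-use pathway that reflects residual liability, in contrasts where SAAF differs between arms and lowers Wave 3 use. The size rests on assumed values: about 16-39% of trials at 100 per group for the larger SAAF effects and 6-13% for the smaller one, higher if arms are pooled. The same logic applies to the SAAF-targeted process mediators. No size is given for them, because the shared-cause correlation left after pretest control is unknown.

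Three stronger readings are not supported. A reader might infer that Aim 2 will usually report a false pathway; at the stated group size and under these assumptions it does so in a minority of trials. A reader might infer that all of a youth's stable liability is counted as early-use effect; only the part missed by the controls is. A reader might infer that the case for dual or preadolescent delivery falls; the Aim 1 comparisons are randomised, and Aim 3 takes its effects from Aim 1.

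**What to change.** In the Aim 2 section:

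1. Name the Wave 1 covariates and put them in both the mediator and the outcome equation, whichever mediator is tested: self-regulation, prototypes of alcohol-using peers, resistance efficacy, parenting, caregiver income, education and household structure. All are already planned; for example, the demographics section states "Primary caregivers will report their yearly income, per capita income, employment status".
2. For each indirect effect declared, report the residual mediator-outcome correlation that would reduce it to zero, and state the pathway as conditional on no larger unmeasured confounding. In the 60% example that correlation is .24/.64 = .375. This step is needed because the covariates reduce the bias without removing it.
3. Show the Aim 1 total effect beside each indirect effect.

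A sensitivity model separating a youth-level random intercept from the repeated alcohol waves is optional; with sparse binary use it is one choice among several.

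The cost is SAP wording and some extra analysis, with no new data. The downside is that some mediation claims will be weaker.

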### **Repeated assessments and attrition.**

Families will participate in 5 annual assessments. Wave 1, the baseline assessment will occur when youth are age 11 and approximately 3 months prior to implementation of SAAF. Wave 4 will occur just prior to the implementation of the SAAF–Teen. The final assessment, Wave 5, occurs approximately 10 months after implementation of SAAF—Teen. In previous

basic research and prevention trials

conducted at CFR, 5-year retention

rates ranged from 88% to 92% .

We plan conservatively for a 13%

attrition rate, ensuring that 400

[figure not shown]

participants (87% of 460) will complete the trial. Figure 5 presents the project timeline.

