#### **Retention of trial participants.**

CFR retention protocols have yielded high retention rates with African American

families followed for time periods ranging from 3 to 14 years. At each data collection, family members provide contact information for three or more individuals who will always know their whereabouts. We gather email addresses, cell phone numbers, and Internet social networking addresses for participants and their primary contacts. Following each data collection visit, project staff contact participants to inquire about the quality of the experience, confirm contact information, and answer questions. Between data collections, we phone participants every 3 months to update contact information. Participants also receive a project newsletter that includes a stamped address correction form, as well as birthday cards and holiday cards. Experienced retention staff work with participants' contacts, CLs, and commercial databases such as NetDetective to locate lost participants. Participants' 5-year rates of mobility outside of Georgia are low (~3%). At each follow-up, we are prepared to send a data collection team to participants' homes throughout the region to collect data from families who have moved. For participants who leave the region, we collect data by phone or online; our research teams have experience with both modes of data collection.

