**Alcohol and other drug use (Waves 1-5).**

The substance use assessment is designed to address the multidimensional nature of use. Items were selected from three well-validated measures for their sensitivity to intervention effects in our previous research at several levels of substance use. At the initiation level, group differences in the proportion of participants who transition from nonuse to use during the study can be detected. At the escalation level, group differences in the proportion of participants who increase their frequency/intensity of use during the study can be assessed. At the problem use level, group differences in specific substance-related behaviors and problems can be indexed. The basic items in the measure are those included in the Monitoring the Future study, which assess lifetime, annual, and 30-day prevalence and frequency of cigarette smoking, alcohol use, binge drinking, and marijuana use. For the purposes of the proposed study, a 3-month assessment will be added. A checklist of other drugs includes lifetime use of LSD/acid, Ecstasy, cocaine, heroin, other opiates, amphetamines, non-prescribed tranquilizers, and inhalants. Problems associated with substance use will be indexed using items from the Minnesota Student Survey for high school students and the Rutgers Alcohol Problems Index. These scales include items assessing dependence (e.g., had to use more to get same effect, tried to cut down but couldn't) and negative consequences of use (e.g., hurt relationships with friends or family, interfered with other activities, resulted in legal problems, missed school or work).

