**SAAF Targeted Protective Practices (Waves 1-3).**

The SAAF Intervention-Targeted Processes instrument assesses parenting and individual youth processes on which SAAF sessions focus. The battery includes parallel versions of items that permit youth and parents to report the frequency of parenting practices and parent-youth relationship dynamics we termed *regulated/communicative parenting*. Items include those from well-established measures of relationships climate, disciplinary practices, and racial socialization processes that were adapted for African American families with the assistance of focus groups, as well as items specifically written for the SAAF trial and validated with those data. Subscales, confirmed via factor analysis, include involved vigilant parenting, racial socialization, and clear expectations about alcohol use and other risky behavior. Items assess behavior in the past 6 weeks with responses that range from 1 (*never*) to 5 (*always*). Cronbach's alphas for the subscales ranged from .70-.92 in our prior prevention research and were sensitive to intervention participation. Items assessing youths' *intrapersonal protective processes* targeted in SAAF include the following subscales: *behavioral and emotional self-regulation, racial identity, prototypes of alcohol-using peers, and resistance efficacy*. Youth report their intrapersonal protective processes and parents report their observations of youths' self-control. As with the family items, these scales were developed from existing items, adaptations derived from focus group feedback, and specific items written for the SAAF trial. They were confirmed with factor analyses, and Cronbach's alphas ranged from .68-.90.

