**SAAF-Teen Targeted Protective Practices (Waves 4 and 5).**

The SAAF-Teen Intervention-Targeted Protective Processes instrument (see Appendix D for all items) assesses parenting and individual youth processes on which SAAF-Teen sessions focus. As with the SAAF instruments, the SAAF-Teen battery includes parallel versions

of items that permit youth and parents to report the frequency of developmentally appropriate parenting behaviors that we termed *competence-promoting parenting*. Many items represent developmentally appropriate items, adapted via wording changes and behavioral emphases, of items used in SAAF (limit setting, consistent discipline) as well as new items that address unique intervention targets such as parents' provision of support and coaching for dealing with discrimination and for planning academic and vocational careers. Additional items address parental involvement in youths' educational pursuits and problem-solving interactions that foster youths' sense of autonomy and competence. Youth subscales emphasize goal setting and planning; self-regulatory processes and skills for coping with stress, particularly racial discrimination; and decision-making processes in peer contexts. Subscale reliability ranged from .70-.92 in our prior prevention research, and the scales were sensitive to intervention participation .

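### For the SAAF-Teen pathway in Aim 2, the only post-programme mediator and alcohol values come from the same Wave 5 visit, so the planned indirect effect cannot be separated from reverse or shared causes

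*Combined protocol and SAP*

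**What the plan says.** Aim 2 states its purpose as follows: "This aim examines pathways through which different inoculation strategies affect distal (W5) alcohol use". It names three sets of candidate mediators: SAAF-targeted processes, SAAF-Teen-targeted processes, and Wave 3 alcohol use. Earlier levels of mediator and outcome are controlled throughout. For SAAF-Teen processes the text is specific: "pretest (Wave 4) levels of these processes will be controlled when testing for posttest (Wave 5) changes". Indirect effects are tested by bootstrapping.

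The timing is in the section on repeated assessments and attrition. "Wave 4 will occur just prior to the implementation of the" SAAF-Teen programme, and "The final assessment, Wave 5, occurs approximately 10 months after implementation of" it. Under Measures, SAAF-Teen processes are collected at Waves 4 and 5, SAAF processes at Waves 1-3, and alcohol use at all five waves.

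The Aim 2 text gives no assumption about the order of processes and drinking between Waves 4 and 5, and none about unmeasured common causes. It plans no reversed model and no sensitivity analysis for this path.

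**The concern.** Randomisation protects the path from assignment to processes. It does not protect the path from processes to alcohol, which is observational and needs either time order or an explicit assumption. For SAAF-Teen there is no time order after the programme, because mediator and outcome are read at one visit.

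Drinking that begins or rises after Wave 4 can itself alter parental monitoring, conflict or self-regulation as reported at Wave 5. A third influence arising in that interval can move both. When the youth reports both, shared reporting adds to the correlation. Any of these, combined with a programme effect on processes, gives a non-zero product of paths. The bootstrap then tests whether that product differs from zero, not which way the second path runs.

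At stake is what the trial may say about how SAAF-Teen works, alone or as the second inoculation. The randomised Aim 1 comparison is not touched.

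**Working it through.** **1. Timing, set side by side**

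| Mediator set | Measured | Before the Wave 5 outcome? |
|---|---|---|
| SAAF processes | Waves 1-3 | yes |
| Alcohol use as mediator | Wave 3 | yes |
| SAAF-Teen processes, post-programme | Wave 5 | no, same visit |

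**2. The plan's own Aim 2 figure**

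The plan states power of .7 to .9 for paths of .2 to .4 with 100 per group. Simple versions give these powers for paths of .2 / .4:
- Standardised path, N = 100: .52 / .99
- Standardised path, N = 200: .82 / above .99
- Standardised path, N = 400: .98 / above .99
- Two-group difference, 100 per side: .29 / .81

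None gives .7 to .9. The plan does not list the values at which it held the other model parameters, so its figure can be neither confirmed nor called wrong. It does not bear on this point, because power to detect a path says nothing about its direction.

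**3. What the planned regression estimates when the true path is zero**

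Let T be assignment (0/1), M the processes, Y alcohol use, and r the effect of drinking on processes. Suppose

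Y5 = 0.4·Y4 − 0.2·T + e_Y, with no effect of M

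M5 = 0.5·M4 + a·T − r·Y5 + e_M

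Given T, M4 and Y4, with unit residual variances, the slope of Y5 on M5 tends to −r / (1 + r²):
- r = .1: −.1 / 1.01 = −.099
- r = .2: −.2 / 1.04 = −.192
- r = .3: −.3 / 1.09 = −.275

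A purely reverse effect therefore yields nearly the slope that a genuine path of the same size would give. Controlling Wave 4 levels is already built into this result.

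The path from T to M5 is a + 0.2·r. If a = 0 and r = .3 it is only .06, which is why the false rate stays low when SAAF-Teen has no direct effect on processes.

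**4. How often mediation is declared with no true process-to-alcohol effect**

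Simulation of the model above used 100 per side and required both paths at p < .05. Ranges cover unit and standardised residual variances.

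| Direct SAAF-Teen effect on processes (a) | r = .1 | r = .2 | r = .3 |
|---|---|---|---|
| 0.4 SD | 25-30% | 66-78% | 86-94% |
| 0.2 SD | 9-14% | 29-38% | 43-50% |
| none | 2-8% across r = .1 to .3 | | |

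A second simulation replaced the reverse effect with a residual Wave 5 correlation of .1 / .2 / .3. It assumed Wave 4-5 stability of .5 and a Wave 4 process-alcohol correlation of .2.
- 0.4 SD: 26% / 73% / 89%
- 0.2 SD: 10% / 29% / 37%
- No programme effect on processes: at most about 5%

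Genuine mediation at 0.4 SD with a path of .2 / .3 was declared in 73% / 89% of runs, the same as the false rate. With 200 per side (the two SAAF-Teen arms against the other two), the false rate at 0.4 SD runs from 50% to 99.6%, so a larger sample does not help.

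A percentile bootstrap of the product agreed with the two-path test within 2 percentage points in six scenarios.

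**The case against.** **Wave 4 data exist.** A reader might infer that mediator and outcome are measured only at Wave 5, or that Aim 2 as a whole cannot distinguish mediation from reverse causation. The documents support neither. SAAF-Teen processes are also measured at Wave 4 and alcohol at every wave, and two of the three mediator sets precede the outcome. Because earlier levels are controlled, only the residual Wave 5 association matters. This narrows the point to one pathway but does not remove it.

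**The rates rest on assumed inputs.** This is correct. The documents give no SAAF-Teen effect on processes in SD units and no drinking-to-process coefficient. A reader might infer that a false pathway will readily be declared. That needs SAAF-Teen to move the processes and some residual correlation to remain. The plan does expect movement, since it reports that the scales responded to participation in prior work. The simulations also use a normal outcome, whereas Aim 1 allows logistic and count models.

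**Recall windows.** It is tempting to say that much of the drinking window precedes the mediator window. The SAAF instrument states "Items assess behavior in the past 6 weeks", but no window is stated for the SAAF-Teen items, so no such percentage can be derived.

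**Parallel caregiver reports.** These exist for parenting behaviours and limit shared-reporter bias to models using youth report. They do not settle direction.

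**Conclusion.** The point holds for the SAAF-Teen pathway only. The measurement schedule alone shows that post-programme mediator and outcome are concurrent, and nothing in the planned analysis orders them. Figure 7 is not shown in the text available, but a path diagram cannot change when the data are collected.

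The size is conditional. At r = .1 to .3 with 100 per side, false mediation is declared in roughly 25-94% of trials at 0.4 SD, 9-50% at 0.2 SD, and 2-8% with no direct programme effect on processes. The last range assumes that the programme lowers alcohol use by 0.2 SD. With an alcohol effect of up to 0.4 SD and a reverse coefficient of up to .4, pure reverse causation gives 1.5-24%. These are illustrations over assumed inputs, not forecasts for this trial. The firmer statement is that a significant SAAF-Teen indirect effect would look much the same whether the path is real or not.

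**What to change.** Amend the Aim 2 text for models that use Wave 5 SAAF-Teen processes with Wave 5 alcohol use:

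1. Report the indirect effect as a concurrent, exploratory association and not as established mediation. State the ordering and no-confounding assumptions on which a causal reading would depend.
2. Show it beside the reversed model, with Wave 5 alcohol use as the intermediate and processes as the outcome. The reversed model does not settle direction; it shows readers whether the data fit both.
3. Add a sensitivity analysis over the residual Wave 5 process-alcohol correlation, giving the value at which the indirect effect is no longer distinguishable from zero.
4. Prefer caregiver-reported processes where they are available.

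The cost is two extra analyses on data already planned and a weaker claim for this pathway. The SAAF and Wave 3 alcohol pathways need no change on this account.

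An interim process assessment is not asked for. The plan does say "Between data collections, we phone participants every 3 months to update contact information", but scales for youth and caregivers would be a new data collection, with consent, payment and a change from computer-assisted self-interview. It would also reduce the problem without removing it. With a 0.4 SD programme effect and alcohol stability of 0.6, false mediation was still 9% / 25% / 46% for reverse coefficients of .1 / .2 / .3.

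### Aim 2 controls Wave 4 as a pretest in the SAAF-Teen mediator models, although Wave 4 is a post-randomisation outcome of SAAF; contrasts that cross SAAF assignment lose any carry-over from SAAF

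*Combined protocol and SAP*

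**What the plan says.** All references are to the combined protocol and SAP.

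- **Adjustment rule (Aim 2).** The general rule is that "Baseline or pretest levels of distal and proximal processes will be controlled in all analyses". The worked example takes SAAF-Teen-targeted processes as the mediator: "pretest (Wave 4) levels of these processes will be controlled when testing for posttest (Wave 5) changes". Neither sentence limits the rule to particular arm contrasts.
- **Randomisation (Random assignment and contamination).** It happens once: "After pretest, families will be assigned randomly to one of four experimental groups". "The dual-inoculation group will be assigned to receive both SAAF at age 11 and SAAF–Teen at age 14".
- **Timing (Repeated assessments and attrition).** "Families will participate in 5 annual assessments". Wave 1 is "approximately 3 months prior to implementation of SAAF", and "Wave 4 will occur just prior to the implementation of the" SAAF-Teen.
- **Instruments (Measures).** The SAAF process battery is collected at Waves 1 to 3 and the SAAF-Teen battery at Waves 4 and 5 only. Many SAAF-Teen items are described as adaptations of SAAF items, with limit setting and consistent discipline as examples.
- **Notice (Random assignment and contamination).** Families do not learn whether they will receive SAAF-Teen "until several months prior to its implementation".

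**The concern.** A pretest covariate is safe when treatment cannot have affected it. Wave 4 meets that condition for SAAF-Teen, leaving notice aside, but not for SAAF. For two of the four arms it is a follow-up measure taken after one of the randomised programmes. Because the two batteries share content, SAAF could plausibly move the Wave 4 score.

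Aim 2 asks how the different inoculation strategies reach Wave 5 alcohol use. In the SAAF-Teen mediator models, the path from assignment to the Wave 5 process is the first leg of the indirect effect. If Wave 4 is held constant in a comparison of a SAAF arm with a non-SAAF arm, whatever SAAF contributed through Wave 4 is taken out of that leg. The dual arm then tends to look like the mid-adolescent arm, which hides the carry-over that would set two inoculations apart from one. Conditioning on Wave 4 also opens a path through any unmeasured family factor that drives both waves. A larger sample cures neither problem.

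**Working it through.** **The plan's own figure.** The only number in Aim 2 is power of .7 to .9 for paths of .2 to .4 with n = 100 per group. A simple Fisher-z calculation (two-sided .05) for paths of .2, .3 and .4 gives .52, .86 and .99 at N = 100, and .81, .99 and 1.00 at N = 200. Neither set matches, but the plan's result is a Monte Carlo one and its fixed parameters are not given, so it can be neither reproduced nor refuted. The present point does not depend on it.

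**Timing.** With annual waves, Wave 4 is Wave 1 + 36 months. SAAF starts at about Wave 1 + 3 months. So Wave 4 is about 36 − 3 = 33 months after SAAF starts.

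**Formula.** For any two arms (ANCOVA identity):

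adjusted Wave 5 contrast = unadjusted contrast − γ × (difference between arms in mean Wave 4),

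where γ is the within-arm slope of Wave 5 on Wave 4. If SAAF shifts Wave 4 by *a*, and notice of SAAF-Teen has no effect, the loss is γ*a* in the four contrasts that cross SAAF assignment and zero in the two that do not.

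**Range of the loss.** The documents give neither *a* nor γ, so both are assumed. The entries are γ × *a*, in SD:

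| *a* | γ = .4 | γ = .5 | γ = .6 | γ = .7 |
|---|---|---|---|---|
| 0 | 0 | 0 | 0 | 0 |
| .1 | .04 | .05 | .06 | .07 |
| .2 | .08 | .10 | .12 | .14 |
| .3 | .12 | .15 | .18 | .21 |
| .4 | .16 | .20 | .24 | .28 |

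**Worked case.** Assume *a* = .3, causal carry-over from Wave 4 to Wave 5 *s* = .5, SAAF-Teen effect .2, and no direct SAAF effect on Wave 5. The unadjusted SAAF effect is .5 × .3 = .15. With no common cause, γ = *s* = .50 and the loss is .15. With a stable unmeasured trait that makes up 40% of Wave 4 variance and carries on to Wave 5, γ = .5 + (1 − .5) × .4 = .70 and the loss is .21.

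| Contrast | Unadjusted | Adjusted, γ = .50 | Adjusted, γ = .70 |
|---|---|---|---|
| Preadolescent vs control | .15 | .00 | −.06 |
| Dual vs mid-adolescent | .15 | .00 | −.06 |
| Dual vs control | .35 | .20 | .14 |
| Preadolescent vs mid-adolescent | .15 − .20 = −.05 | −.20 | −.26 |
| Dual vs preadolescent | .20 | .20 | .20 |
| Mid-adolescent vs control | .20 | .20 | .20 |

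OLS on simulated four-arm data (200,000 per arm) agreed with these values to about .005. The preadolescent vs mid-adolescent row was not simulated and comes from the identity alone.

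In the γ = .50 column, dual vs control equals mid-adolescent vs control (.20), so the SAAF component has disappeared.

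**When the sign reverses.** With a direct SAAF effect *d*, the adjusted SAAF effect is *d* + *sa* − γ*a* = *d* − (γ − *s*)*a*. In the worked case (γ − *s*)*a* = .20 × .3 = .06, so the sign reverses only if *d* is below .06. With *d* = .1, the effect falls from .25 to .04 without reversing.

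**Notice, taken separately.** If notice of SAAF-Teen shifted Wave 4 by an assumed .1 SD, then with γ = .70 both dual vs preadolescent and mid-adolescent vs control would go from .20 + .5 × .1 = .25 to .25 − .70 × .1 = .18. That is a bias in the SAAF-Teen effect.

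**The case against.** The best defence is that the sentence is an example about what SAAF-Teen changed between Waves 4 and 5, and for that question Wave 4 is the natural pretest. This stands for mid-adolescent vs control and dual vs preadolescent. It does not settle the other four contrasts. The preceding sentence applies the rule to all analyses, and because the SAAF-Teen battery has no Wave 1 value, the only pretest available for that mediator is Wave 4.

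A second defence is that the general model is in Figure 7, which is not shown in the text available. In an SEM, controlling Wave 4 could mean a Wave 4-to-Wave 5 path with Wave 4 itself regressed on assignment. SAAF's indirect effect could then be recovered, at least in part. This is possible, but the text says only that Wave 4 is controlled, and a common cause of the two waves would still bias the separate paths.

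Third, the sizes rest on assumptions. That stands in full: after about 33 months SAAF may not move Wave 4 at all, and then nothing is lost.

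A reader might infer more than the documents support:

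- **That Aim 2 as a whole, or the main trial results, are compromised.** Aim 1 is not stated to adjust for Wave 4, and Aim 3 takes its effects from Aim 1. SAAF-targeted processes and Wave 3 alcohol use are separate mediators that the Wave 4 example does not concern.
- **That late notice is part of why SAAF's contribution is lost.** It is not. Notice would affect the SAAF-Teen effect, and its order relative to the Wave 4 visit is only inferred from undated wording. The reminder at home visits that families may still be selected (Intervention engagement and re-engagement) does not say whether the Wave 4 visit is included.

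**Conclusion.** The point holds for the Aim 2 models with SAAF-Teen-targeted processes as mediator, in four contrasts: dual vs control, dual vs mid-adolescent, preadolescent vs control, and preadolescent vs mid-adolescent. There, the Wave 4 adjustment conditions on an outcome of SAAF and removes γ × *a* from the Wave 5 process contrast. That is 0 if SAAF leaves Wave 4 unchanged, and .04 to .28 SD over the assumed ranges. The direction of the problem follows from the design; its size is not known from the documents. Sign reversal is a possibility, not a prediction: it needs unmeasured causes shared by Waves 4 and 5 and a small direct SAAF effect.

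The order of notice and the Wave 4 visit is a separate and secondary query. The wording suggests that notice may come first, which could bias the SAAF-Teen effect even in the two contrasts where Wave 4 adjustment is otherwise sound.

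**What to change.** In the Aim 2 text:

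1. Name the contrasts in which Wave 4 SAAF-Teen processes are a covariate, and limit them to mid-adolescent vs control and dual vs preadolescent.
2. In the four contrasts that cross SAAF assignment, adjust for the Wave 1 SAAF battery and Wave 1 alcohol use. A Wave 1 value of the SAAF-Teen battery does not exist, so these are the available pre-randomisation measures.
3. In those contrasts, regress Wave 4 on assignment as a post-SAAF mediator and report the total effect on the Wave 5 process.
4. Add a sensitivity analysis for unmeasured Wave 4-Wave 5 confounding. Step 3 recovers the total effect, but the separate direct and indirect paths stay open to that bias.

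Separately, reconcile the notice wording in Random assignment and contamination with the Wave 4 timing in Repeated assessments and attrition, and record for each family whether notice came before or after the Wave 4 visit.

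The analysis changes need wording only and no new data. Their price is some loss of precision in the four contrasts that give up Wave 4 as a covariate.
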